## Abstract

Chronic pain is prevalent among U.S. military personnel and often accompanied by comorbid behavioral health disorders and other medical conditions that further complicate its management. According to the Centers for Disease Control and Prevention, the prevalence of chronic pain among active-duty Service members is 1.5 to 2 times higher than the 20% of American adults who live with chronic pain. Recent report findings determined that Service members make up a large population within the Military Health Systems (MHS), and that this population is disproportionately affected by lost duty days, early retirement, loss of readiness, and increased burden to the MHS. To date, the Department of Defense (DOD) and MHS have emphasized multimodal, multidisciplinary, stepped treatment for chronic pain that prioritizes nonpharmacologic therapies and non-opioid pain medications. Though the DOD and MHS have invested in several pain treatment types, our level of understanding needs to better distinguish between acute and chronic pain and identify risk factors and mechanisms responsible for the chronification of pain, as it is the chronic pain which compromises functioning and readiness to a greater degree across the force. The novel information generated by this study will enhance our understanding of how ankle fracture elicits pathological risk factors for bone fracture associated neuropathic pain (BFNP), which ultimately impairs health-related quality of life. Due to the high prevalence of ankle fractures and the subsequent risk of developing chronic pain after ankle fracture, we will utilize this patient population to provide the preliminary evidence on whether bone fracture and subsequent BFNP phenotypes are reflected in specific genetic profiles and activated states of immune cells.

## Introduction

Persistent pain, such as neuropathic pain (NP), is an outcome of ankle fracture repair with incidence rates 1-year post-surgery of 18–42% [1]. Ankle fractures are one of the most common surgically-treated fractures in adults with the greatest incidence occurring in young males [2]. In general, three stages of pain follow a bone fracture including acute, subacute and chronic pain. Acute pain occurs immediately after injury. After about a week or two, the worst pain is usually subsiding as the fractured bone and the surrounding soft tissue begin to heal. Many individuals may continue to report pain during this subacute period. Pain that persists after fracture union has taken place is called chronic pain. Chronic or persistent NP is one of the worst, longest-lasting, and difficult symptoms to manage after fracture repair in civilian and military populations [3]. Some of the pathophysiologic mechanisms leading to NP likely propagate early after injury, providing opportunity for early interventions.

Neuropathic pain-associated with bone fracture likely originates from a lesion affecting the somatosensory nervous system and may be associated with abnormal sensations, called dysesthesia, or pain from normally non-painful stimuli (allodynia). The condition may have continuous and/or episodic (paroxysmal) components, with the latter resembling stabbing pain or electric shocks. The condition of NP also tends to affect defined dermatomes and there may be limits to the area of pain. The general working principle is that the lesion leading to pain must directly involve nociceptive pathways [4]. Additional elements which can contribute to NP include sensitization of intact nociceptors that survive injury, which innervate the region affected by the injured nerve fibers and contribute to spontaneous activity. These changes in the intact nociceptors may induce ongoing pain and account for certain aspects of hyperalgesia [5]. Conditions associated with bone fracture-associated NP (BFNP) include traction neuropathy, nerve compression from soft tissue edema, bone fragment, implants, and hematoma [6,7].

In civilian adult populations, prevalence rates of NP are about 1 in every 10 adults over age 30, though the prevalence rate and people identified vary depending on the method of identification of NP [8,9]. Given the number of active duty personnel and Veterans who experience pain due to injury, the US military instituted a number of programs, guidelines and initiatives to better manage acute pain for combat-related injuries [10]. Despite the instituted practices by the military, NP after fracture remains a major problem, and literature documenting detailed outcomes of BFNP is scarce.

Chronic bone injury sequelae, which may contribute to BFNP, include the release of factors that excite and sensitize sensory nerves including neurotransmitters, cytokines/growth factors and receptors, upregulation of sensory neuron ion channels, induction of nerve fiber sprouting in bone tissue, and central sensitization in the brain which can amplify pain signals [11–14]. More recent computational approaches suggest that it is also possible that networks of biomarkers exist that could accurately identify individuals at high risk of BFNP. These biomarkers may exist at the time of injury and are likely accessible at early time points in fracture care. Changing the standard of care treatment for BFNP by identifying at-risk patients early after injury could lead to decreased economic burden in treating BFNP and mitigation of the substantial decrease in quality of life these patients experience.

The primary aims of this longitudinal study are: (1) To evaluate how dysfunctional endogenous pain modulation and increased pain sensitivity will be associated with increased risk for development of BFNP and (2) to identify peripheral blood immune cell biomarkers for BFNP. The hypothesis of this study is that bone fracture will induce dysfunctional endogenous modulation of pain (i.e., increased peripheral and central sensitization) and a long-term systemic alteration of the innate immune system, both of which may increase the risk for NP in bone fracture patients who develop BFNP compared to bone fracture patients who do not develop chronic pain and healthy controls (Fig 1). Once these differences are quantified and biological signaling pathway analyzed, we will be able to identify a biosignature, or set of biomarkers, that can be used to identify BFNP susceptibility early after fracture.

**Fig 1 pone.0327605.g001:**
[figure not shown]
Heuristic model linking bone fracture with chronic neuropathic pain.

## Methods

### Study design and setting

This study will utilize a prospective cohort study design (Fig 2). We will enroll participants who have sustained rotational ankle (specifically AO/OTA 44 types A-C [15]) fractures that are treated operatively. Fracture patients will complete clinic assessment sessions at standard of care visits, including their first post-op appointment (2–4 weeks), at 5–9 weeks, at 3–5 months post-operatively, and at a 6–9 months follow-up visit. Clinic assessment sessions will include completion of questionnaires, blood draw, thermal imaging, quantitative sensory testing, and clinical assessment of infection, fracture healing, and radiographic arthritis. Questionnaires will be completed over the phone or in-person at each approximate time point. These visits will allow assessments during the subacute and chronic stages of BFNP. If fracture participants do not show for the in-person standard of care 6-month visit, the participant will be contacted by phone to collect patient reported outcomes (PROs). Along with this, at 1–1.5 years out the patient may be called for self-reported outcomes to assess if patients reporting chronic pain at 6–9 months still have persistent pain. A separate group of 40 uninjured healthy control participants will perform the same assessments during one study session. Enrollment procedures, including assessment of inclusion/exclusion criteria and informed consent, will occur in study session 1. This study was approved by the Indiana University (IU) Institutional Review Board. The study began January 1^st^, 2024 and will be completed on December 31^st^, 2028. We currently have 6 clinical subjects to date and expect to complete enrollment in June 2028. Data collection and results will be completed in 2029. No analysis has been implemented at this time.

**Fig 2 pone.0327605.g002:**
[figure not shown]
Prospective cohort study design.

**Study design.** This study is an observational cohort study of patients with rotational ankle fractures. Patients will be followed longitudinally, with assignment of patients into 3 groups at >6 months after surgery for fracture repair. The distinction between the *Pain* and *No Pain* cohort will be based on the Chronic Pain Grading Scale (CPGS), with a CPGS of 0 at >6 months defining *No Pain* and a CPGS ≥1 defining the *Pain* Cohort. Several pain states may exist in the *Pain* Cohort. The Douleur Neuropathique 4 (DN4) will be used to identify patients with *BFNP* as described in the text. Patients not meeting *BFNP* will be placed in the *Other Pain-state* group (e.g., CRPS, inflammatory pain, arthritis, pain from complications). This group will be further divided into patients with CRPS and those without based on the CRPS Research Criteria. This study will focus on identifying early biomarker signatures that can discriminate between *No Pain* and *BFNP*. Biomarkers include quantitative sensory testing (QST), mRNA expressions and immune cell activation, and thermography.

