### Statistical analysis

#### Data analysis.

Statistical Analyses/Machine Learning will be conducted under the guidance of our biostatistician. Prior to hypothesis testing, descriptive statistics will be computed for each of the outcome measures, e.g., CPM, TS, and immune biomarkers, by time. The spaghetti plot for each measure over time and distributional characteristics (e.g., normality, outliers, and missingness) will be explored. The proper steps (e.g., transformation) will be taken if needed to ensure the assumptions of the procedure for hypothesis testing are met. To address our aims, we will examine differences in pain modulation (TS, CPM) and immune biomarkers among the fracture participants who develop BFNP and those who do not and healthy controls. We expect fracture patients developing BFNP to exhibit (a) enhanced central sensitization and less efficient endogenous inhibition of pain and (b) alterations in immune cell subsets and cell reactivity post-injury and across time when compared to fracture patients who do not develop chronic pain and matched healthy controls. We will use latent growth mixture models (GMM) [45] to classify the patterns of the trajectory for each measurement by evaluating the latent intercept (baseline means) and latent slope (development) into mutually exclusive classes. GMM will then regress those latent variables to the outcome (BFNP, BF no-chronic pain, and Healthy Control) to test the differences of these factors at 2–3-weeks post injury and across time. Trajectories from the GMM (latent intercept and slopes) will be explained by a nominal latent class variable C. The models will include participant characteristics (e.g., age, race, gender, fracture pattern, etc.). When necessary, a quadratic latent growth variable will be tested to fit the GMM model. The models will be evaluated by the model fit indices such as Akaike information criterion (AIC), Bayesian information criterion (BIC), and likelihood ratio test as well as the corresponding profile plots. GMM is a flexible and more accurate method for measuring change than more traditional approaches such as a univariate repeated measures analyses of variance (ANOVA), a multivariate repeated measures ANOVA, or an analysis of covariance.

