#### Supervised machine learning (ML).

Supervised machine learning predictive models will be implemented using the features such as demographic information, blood biomarkers and QST scores of the study participants. Multiple ML predictive models will be developed and tested to assess their performance and efficacy to better predict which participants will be prone to develop BFNP. The predictive models will be trained/validated and tested using information available 2–3 weeks after surgery and data collected at 6–9 months post-surgery. Our implementation of supervised ML predictive models incorporates these steps: 1) A dataset is gathered. The development dataset needs to be representative of the real-world population and must include reasonably large representations of both BFNP and non-BFNP subjects. 2) Quality controls are applied. All data are subjected to a series of tests to ensure the information is valid and the data do not contain anomalies arising from measurement errors. 3) The features to be used for the prediction models are extracted from the development dataset. The feature extraction will be carried out to transform multiple data types into numerical features usable for ML model training. 4) Feature Selection: Using the domain knowledge and ML based feature selection algorithms, the number of input features will be reduced to decrease computation time and to prevent model overfitting.

A specific ML methodology is selected. We have used a variety of machine learning methodologies including Elastic Net (ENET). ENET is a flexible methodology that, based on how penalty functions are set, can implement various specific methodologies such as Least Absolute Shrinkage, Selection Operator (LASSO) and ridge regression. The algorithm performs both feature selection and regularization to enhance the prediction accuracy and interpretability of the statistical model it produces. Support Vector Machines, K-Nearest Neighbors, Random Forest and Gradient Boost are also used in the methodology on the same training/validation/test dataset, to provide comparison points when establishing the performance of the algorithms generated using ENET. Data split is performed. The model is trained and tested using 70/30 split between training (and validation) and testing datasets. The split is stratified so that training and test subsets have the same proportion of BFNP and non-BFNP class labels as that of the input dataset.

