## Discussion

Overall, findings from this longitudinal study will provide a means to identify patients who may be at risk of developing persistent BFNP. Secondly, the profile signatures identified by the multipronged approach in the proposed study will provide important mechanistic insights into understanding factors contributing to the development of BFNP that may help (1) design appropriate treatment paradigms for patients (with currently available pharmacological and non-pharmacological means) and (2) identify appropriate treatment targets (e.g., increasing inhibitory tone and/or decreasing excitability, suppressing immune/inflammatory triggers) for prevention of BFNP after ankle fracture in military and civilian populations.

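### No separate comparison of BFNP with the Other Pain-state group is stated, so a marker of persistent pain in general could be reported as a BFNP marker

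*Protocol article*

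**What the plan says.** The Fig 2 legend (protocol article, Study design) classifies fracture patients at more than 6 months. A CPGS of 0 is No Pain. Patients with pain are split by the DN4 into BFNP and Other Pain-state, the latter including CRPS, inflammatory pain, arthritis and pain from complications. Of Other Pain-state it adds: "This group will be further divided into patients with CRPS and those without based on the CRPS Research Criteria". The legend then sets the focus: "This study will focus on identifying early biomarker signatures that can discriminate between" No Pain and BFNP.

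The same comparator appears in the hypothesis at the end of the Introduction ("bone fracture patients who develop BFNP compared to bone fracture patients who do not develop chronic pain and healthy controls") and in the directional expectation under Data analysis ("when compared to fracture patients who do not develop chronic pain and matched healthy controls"). The model statement lists the outcome levels: "GMM will then regress those latent variables to the outcome (BFNP, BF no-chronic pain, and Healthy Control"). The Missing data section names the same three groups.

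Two phrases are broader. Data analysis also speaks of differences "among the fracture participants who develop BFNP and those who do not and healthy controls". The machine learning section stratifies its split to keep the "same proportion of BFNP and non-BFNP class labels as that of the input dataset".

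On the claims, the second aim is to identify immune cell biomarkers for BFNP, and the Discussion expects that the signatures "will provide important mechanistic insights into understanding factors contributing to the development of BFNP".

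**The concern.** BFNP patients differ from No Pain patients in two respects: they have persistent pain, and that pain screens as neuropathic. A contrast between these two groups cannot tell which of the two a marker follows. Healthy controls do not help, because chronic or ongoing acute pain excludes them (Table 2). The only patients who share the persistent pain but not the neuropathic classification are the Other Pain-state patients, and no stated analysis compares BFNP with them separately.

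This matters most for the immune markers. The omitted group includes inflammatory pain, arthritis and complications, so general inflammation is a plausible rival explanation for a positive result. If such a marker were described as part of a BFNP biosignature, the description would go further than the comparison behind it.

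**Working it through.** **1. Where Other Pain-state patients go, by section**

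| Section | Comparator for BFNP | Other Pain-state |
|---|---|---|
| Fig 2 legend, focus | No Pain | left out |
| Introduction, hypothesis | no chronic pain; healthy controls | left out |
| Data analysis, expectation and model outcome | no chronic pain; healthy controls | left out |
| Data analysis, general sentence | those who do not develop BFNP | may be pooled in |
| Supervised machine learning | non-BFNP | may be pooled in |

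No row gives a separate BFNP versus Other Pain-state comparison.

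**2. Reproducing the plan's own sample size**

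Inputs from Sample size: α = 0.05 (two-sided assumed), power 0.8, ρ = 0.6, group ratio 1:4, d = 0.31 (NPSI) and d = 0.34 (current pain).

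Smaller group: n = (1 + 1/4)(1 − ρ)(1.960 + 0.842)² / d².
- d = 0.31: 1.25 × 0.4 × 7.849 / 0.0961 = 40.8, so 41; total 5 × 41 = 205, as stated.
- d = 0.34: 1.25 × 0.4 × 7.849 / 0.1156 = 33.9, so 34; total 5 × 34 = 170, as stated.

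The planned sizes therefore rest on a variance factor of 1 − ρ = 0.4. Without it the totals would be 515 and 425. Results below are given both ways; the plain version corresponds to a comparison at a single visit.

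**3. Group sizes (partly assumed)**

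The chosen evaluable sample is 213. The size of Other Pain-state is not stated. Sample size cites 34% with pain at month 6 in a limb-fracture cohort, which gives 0.34 × 213 ≈ 72 with pain and 141 without. BFNP at 20% (the 1:4 ratio) is 43, and at 25% (one in four) is 53. Other Pain-state is then 72 − 43 = 29 or 72 − 53 = 19.

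**4. A marker with no neuropathic specificity**

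Suppose the marker is shifted by d = 0.31 in all persistent pain, so the true BFNP versus Other Pain-state difference is zero. The chance of a positive BFNP versus No Pain test is approximately Φ(d/SE − 1.960), with SE = √[f(1/n₁ + 1/n₂)] and f = 1 (plain) or 0.4.

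- 53 vs 141, f = 1: SE = 0.161, 0.31/0.161 = 1.92, power 0.486 (t distribution: 0.482).
- 43 vs 141, f = 1: SE = 0.174, 0.31/0.174 = 1.78, power 0.428 (t: 0.425).
- 53 vs 141, f = 0.4: SE = 0.102, ratio 3.04, power 0.860.
- 43 vs 141, f = 0.4: SE = 0.110, ratio 2.81, power 0.803.

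So about 43–48% plain and 80–86% with the factor. A direct BFNP versus Other Pain-state test would be positive in 5%, the type I error rate.

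**5. Does pooling solve it?**

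Against a pooled non-BFNP group the expected difference shrinks to 0.31 × 141/160 = 0.273 (53 BFNP) or 0.31 × 141/170 = 0.257 (43 BFNP). The same non-specific marker is positive in 32–40% of studies plain, or 66–78% with the factor. With 53 BFNP, the factor, and any-pain shares of 42%, 50% and 60% (42% is the upper 1-year figure in the Introduction; the other two are assumptions), it is positive in 67%, 54% and 38%. Pooling weakens the problem but does not remove it.

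**6. What the extra contrast can deliver**

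At 34% in pain, BFNP versus Other Pain-state is 43 vs 29 or 53 vs 19. The 95% interval half-width, 1.96 × SE, is 0.47–0.52 SD plain and 0.30–0.33 SD with the factor. Power for a truly specific difference of 0.31 is 21–25% plain and 45–53% with the factor. For an assumed 0.5 SD it is 45–54% plain.

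**The case against.** The restriction to No Pain versus BFNP is declared openly and is consistent with the hypothesis. A marker shared with other pain states can still predict the risk of BFNP, which is what the first aim asks, and the mechanisms named in the Discussion (inhibitory tone, excitability, immune or inflammatory triggers) are general ones. A secondary contrast may also sit in a fuller protocol or analysis plan that is not shown.

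Much of this stands. It means the text does not commit the study to a false claim. It does not remove the point, because the article itself lists the outcome levels of the main model and the groups compared, and Other Pain-state is not among them, while the second aim speaks of biomarkers for BFNP.

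Three stronger readings are tempting and are not supported:
- A reader might infer that Other Pain-state patients are kept out of every analysis. The non-BFNP labels and the phrase on those who do not develop BFNP may include them in a pooled comparator.
- A reader might infer that a general pain marker will be misreported. The text supports only that it could be.
- A reader might take a moderate effect such as 0.5 SD, which gives 81–87% with a plain t-test. That effect size is not in the document; the protocol's own planning values are 0.31 and 0.34.

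**Conclusion.** The point holds in limited form. The article states no separate BFNP versus Other Pain-state comparison, and its sections differ on whether these patients are left out or pooled with No Pain. Under either arrangement, a positive result cannot distinguish a marker of neuropathic pain from one of persistent pain in general.

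How often this could mislead depends mainly on the variance assumption: 43–48% or 80–86% at d = 0.31. At d = 0.34 the corresponding ranges are 49–56% and 87–92%. All of these rest on 213 evaluable patients, a two-sided 5% test, and an any-pain share of 34% taken from a different pain measure (today's pain) in another cohort. The CPGS rule counts any non-zero current, worst or average pain at the fracture site, so the real share may be higher. If it were near 25%, there would be almost no Other Pain-state patients when one in four has BFNP.

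It would also be wrong to infer that a marker without a clear BFNP versus Other Pain-state difference is a general pain marker. With 19–29 patients in the smaller group, a non-significant result says little. The sample-size arithmetic is not at fault here. This is a cheap improvement to analysis and wording, not a flaw that invalidates the design.

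**What to change.** 1. State where Other Pain-state patients enter the growth mixture model and the BFNP / non-BFNP machine learning labels, and make the Fig 2 legend, Data analysis and Supervised machine learning sections agree. Make Other Pain-state a separate outcome level.
2. For each marker that differs between BFNP and No Pain, report the BFNP versus Other Pain-state difference with its confidence interval as a secondary estimate.
3. Claim specificity to neuropathic pain only where that interval supports it. Otherwise describe the marker as distinguishing BFNP from no pain, with specificity undetermined, and do not label it a persistent-pain marker.

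Cost: analysis and reporting only. The grouping and the biomarker measurements are already scheduled for all fracture patients, and the article reports that no analysis has been carried out. The downside is real: the contrast is imprecise (about 19–29 Other Pain-state patients if 34% report pain), and the group mixes CRPS, inflammatory pain, arthritis and complications, so even a clear difference needs careful interpretation and some claims will become weaker.
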